### Analyses of primary and secondary outcomes

We will use intention-to-treat analysis, meaning that all participants who are randomized to a condition will be included in the analyses. To test the efficacy of the exercise intervention (i.e. change in primary and secondary outcomes from pre [T0] to post [T6]), we will perform 2x2 repeated measures (M)ANOVAs with condition (exercise versus wait list) as between-subjects factor, and time (pre [T0] versus post [T6]) as within-subjects factor. We will conduct a RM-MANOVA for the three indicators of work-related fatigue together (*Hypothesis 1*). Furthermore, we will conduct separate RM-(M)ANOVAs for respectively self-efficacy (*Hypothesis 2a and 2b*), sleep (*Hypothesis 2c and 2d*), work ability (*Hypothesis 2e*), cognitive functioning (*Hypothesis 2f*), and aerobic fitness (*Hypothesis 2 g*). The Matching Task will be analyzed using a 2x2x2 mixed design ANOVA, with ‘run type’ (switch versus repetition), and time (pre versus post) as within-subjects factors, and condition as between-subjects factor (exercise versus wait list). In all analyses, we are particularly interested in the ‘condition x time’ interaction, because this indicates that the conditions differ from each other with respect to the development of the outcome measure over time. If applicable, significant interactions will be further examined by paired-sample t-tests. Partial eta-squared will be reported as effect size.

Additionally, to obtain more thorough insight into the clinical meaningfulness of the changes brought about by the exercise intervention [81], we will perform a Chi-Square Test to see if the number of participants who score below cut-off scores of fatigue after the intervention period (T6) differs between the intervention and the control condition (emotional exhaustion <2.2 on the UBOS; overall fatigue: <22 on the FAS).

To investigate whether intervention-effects last during the follow-up period, for each primary and secondary outcome measure, a repeated measures MANOVA will be performed to see whether it differs between pre (T0), post (T6), 6 weeks after the intervention period (T7), and 12 weeks after the intervention period (T8). If the overall time effect of MANOVA is significant, post hoc tests will be carried out to exactly determine between what time points the outcome had changed. As follow-up measures are only available for the intervention condition, the control condition will not be included in these analyses.

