Against this background, the aim of the current study is to test the effect of exercise on work-related fatigue with a design that allows for strong causal inferences. To this end, employees with high levels of work-related fatigue who currently do not engage in regular exercise will be randomly assigned to either a six-week exercise intervention or a wait list (control group). This enables us to test the effect of exercise on work-related fatigue compared to the ’natural course’ of these symptoms. In the intervention, we will use running as a form of exercise, because it is easy to implement: only running shoes are needed and it is high in flexibility in terms of time and place. Based on the proposed psychological and physiological working mechanisms and available empirical research, we hypothesize:*Hypothesis 1*: the exercise intervention is effective in reducing work-related fatigue

Additionally, we will measure the impact of exercise on five secondary outcomes, which are relevant for employees with high levels of work-related fatigue, and which may be expected to be positively affected by means of regular exercise.

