### Participants and recruitment

Participants will be employees reporting high levels of work-related fatigue. Every employee – regardless job position – can sign up for participation. Participants will be recruited through advertisements with study information in personnel magazines, on facebook pages, and on intranet of large organizations in the region(s) in which the intervention will be carried out. Furthermore, advertisements and news items will be placed in (local) newspapers and on social media.

Inclusion criteria will be based on existing cut-off scores on two validated measures of work-related fatigue: a) ≥2.2 on the emotional exhaustion scale of the Dutch version of the Maslach Burnout Inventory [49]; b) ≥22 on the Fatigue Assessment Scale [50]. Participants can fill out these two scales on the study website (www.runtervention.nl). When participants score high on both scales, the researcher ([name]) will ask these participants for further information about exclusion criteria by email. Exclusion criteria will be: a) ≥ one hour exercising a week; b) fatigue attributable to a medical condition; c) currently or in the past six months receiving psychological and/or pharmacological treatment; d) drug dependence; e) contraindications to exercise. Contraindications to exercise will be measured by the Physical Activity Readiness Questionnaire (PAR-Q; [51]). Eligible participants will be invited for an appointment with the first author ([name]) or research assistants. During this appointment, the baseline measures (T0; except for the two measures of work-related fatigue that are already filled out) will be completed, the cognitive performance tests will be done, and the randomization procedure will be carried out. A separate appointment will be planned for the aerobic fitness test.

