### Primary outcome measures

#### Work-related fatigue

We will use three self-reported indicators to measure work-related fatigue. First, *emotional exhaustion* will be assessed with the subscale ‘Emotional exhaustion’ of the Dutch adaptation of the Maslach Burnout Inventory [58], the Utrecht Burnout Scale (UBOS [59]). The scale consists of 5 items, for example “I feel burned out from my work” (0 = *never*, 6 = *every day*). A mean score equal to or higher than 2.2 on this scale is defined as a ‘high level’ of work-related fatigue [59]. Previous research shows that psychometric properties of this scale are good [60]. Secondly, *overall fatigue* will be measured with the 10-item Fatigue Assessment Scale (FAS [50]). An example question is “I get tired very quickly” (1 = *never*, 5 = *always*). A sum score higher than 21 is indicative of a high level of fatigue [61]. The scale has found to be valid and reliable [50]. Third, *need for recovery* will be assessed by a short version of the ‘Need for Recovery Scale’ [62]. The scale consists of 6 items. An example item is: “Because of my job, at the end of the working day I feel rather exhausted” (1 = *(almost) never*, 4 = *(almost) always*). For this scale, no norm scores are available. Therefore, inclusion was based on the measures UBOS and FAS. Previous research shows that validity is good [62].

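### Hypothesis 1 is judged by one joint test that an effect on the overall-fatigue scale alone can make significant, and the stated follow-up is within-arm only

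*Protocol article*

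**What the plan says.** Hypothesis 1 (Background, Exercise and work-related fatigue) is that "the exercise intervention is effective in reducing work-related fatigue". Under Primary outcome measures the protocol says "We will use three self-reported indicators to measure work-related fatigue": emotional exhaustion (UBOS), overall fatigue (FAS) and need for recovery.

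The FAS is described in two ways. Participants and recruitment counts it among "two validated measures of work-related fatigue". Under Primary outcome measures, overall fatigue "will be measured with the 10-item Fatigue Assessment Scale". The example item there is "I get tired very quickly", and the cut-off is explained as "A sum score higher than 21 is indicative of a high level of fatigue". The UBOS cut-off in the same paragraph is tied explicitly to work-related fatigue. The example items for emotional exhaustion and need for recovery both name work or the job. Table 1 lists overall fatigue as one of the indicators under work-related fatigue.

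For the test, Analyses of primary and secondary outcomes says "We will conduct a RM-MANOVA for the three indicators of work-related fatigue together" and points to the condition x time interaction. Significant interactions are examined, if applicable, by paired-sample t-tests. Chi-square tests of the UBOS and FAS cut-offs at T6 are added to judge clinical meaningfulness.

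**The concern.** A multivariate condition x time test asks whether the arms differ in change on at least one of the three scales. It does not say which one. The intervention is a running programme that is also expected to raise aerobic fitness (Hypothesis 2g), so people might tire less quickly without any change in exhaustion from work. If that were the only effect, the joint test could still be significant and Hypothesis 1 would count as supported.

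The stated follow-up does not settle the question. A paired t-test compares T0 with T6 within one arm. It cannot show that the arms differ on a given scale, and it does not separate an intervention effect from the natural course that the wait list is there to measure. The chi-square tests do compare arms, but they are supplementary, they dichotomise, and they leave out need for recovery. At stake is whether the headline conclusion about work-related fatigue follows from the test that produces it.

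**Working it through.** **Inputs from the protocol (Sample size; Randomization and blinding).** 90 analysable participants at 1:1, so 45 per arm; two-sided 5% level; effect size f = .15.

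**Assumptions.** The protocol gives no correlations between the three change scores. They are taken as equal for all pairs, r = .3, .5 or .7. Effects are between-arm differences in change, in SDs of change.

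**The plan's own figure, and the effect size it implies.** For the repeated-measures interaction with two arms and two occasions, λ = f² × N × 2/(1 − ρ). With ρ = .5 this gives N = 90 (power 0.804). With the printed ρ = .05 it gives N = 168 (power 0.53 at N = 90). That discrepancy is a separate matter. It is used here only to anchor d. Setting λ = (N/4)d² gives d = 2f√(2/(1 − ρ)):
- ρ = .5: d = 0.30 × √4 = 0.60.
- ρ = .05: d = 0.30 × √2.105 = 0.435.

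**Joint test with an effect on the FAS only.** The 2x2 RM-MANOVA interaction is Hotelling's T² on the three change scores: noncentral F with 3 and 86 df, λ = (N/4) d′R⁻¹d. With zero effect on the two work-anchored scales,

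λ = 22.5 × d² × (1 + r)/[(1 − r)(1 + 2r)].

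The last factor is 1.161, 1.500 and 2.361 at r = .3, .5 and .7. For d = 0.6, 22.5 × 0.36 = 8.1, so λ = 9.40, 12.15 and 19.13. For d = 0.4, 22.5 × 0.16 = 3.6, so λ = 4.18, 5.40 and 8.50.

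| FAS-only effect | r = .3 | r = .5 | r = .7 |
|---|---|---|---|
| 0.4 SD | 36% | 45% | 66% |
| 0.435 SD | 42% | 53% | 74% |
| 0.6 SD | 71% | 83% | 96% |

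Simulation of the 0.6 SD case reproduces the last row. It also shows the joint test significant, with neither work-anchored scale differing between arms at 5%, in about 62%, 73% and 88% of trials.

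**The joint test cannot tell the patterns apart.** If all three scales move by 0.6 SD, λ = 22.5 × 3 × 0.36/(1 + 2r). At r = .5 this is 12.15, the same as for the FAS alone, so both situations reject in 83% of trials.

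**Option A: drop the FAS from the test** (two scales, 2 and 87 df, λ = 22.5 × 2d²/(1 + r)). If all three move by 0.6 SD, power is 88%, 83% and 78%, against 91%, 83% and 75% with three scales. If the work-anchored scales move by 0.3 SD and the FAS by 0.6 SD, power falls from 67%, 64% and 69% to 32%, 28% and 25%.

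**Option B: keep the joint test and also require a work-anchored scale to differ between arms** (two-sided 5% per scale, expected direction; simulated, 100,000 runs per setting, r = .3, .5, .7).
- FAS-only effect of 0.4 or 0.6 SD: work-related fatigue wrongly claimed in about 4% of trials.
- All three move by 0.6 SD: 89%, 82% and 74%, against 91%, 83% and 75% for the joint test alone, a loss of about 1 to 2 points.
- Work-anchored scales 0.3 SD, FAS 0.6 SD: 41%, 38% and 36%, against 67%, 64% and 69%, a loss of about 26 to 33 points.

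**The case against.** The strongest reply is that the authors define their outcome: the FAS is deliberately one of three indicators of work-related fatigue in the recruitment section, Table 1 and the outcome section. On that definition the test matches the outcome, and whether a general scale belongs in the construct is a measurement judgement. Only one of the ten FAS items is shown. This stands to the extent that it rules out a stronger reading, namely that the FAS is invalid here or must leave the primary test. The documents do not support that, and Option A shows that removal could be expensive. It does not remove the mismatch between labels or make the joint test specific to work.

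Entry requires high scores on both the UBOS and the FAS and excludes fatigue due to a medical condition. This narrows the construct gap at baseline, but it does not tie a later FAS change to work.

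The FAS-only scenario is constructed. The mechanisms proposed in the Background include coping with work stress and detaching from work, which would act on the work-anchored scales. The running is of low intensity and lasts six weeks. So the percentages are conditional, and nothing in the protocol says that this pattern is likely. The 0.6 SD anchor also needs ρ = .5 rather than the printed .05.

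Details of how a joint test is broken down are often left to an analysis plan. Here, however, the article itself names the follow-up, and what it names does not compare the arms. The chi-square tests may reveal a FAS-only pattern, but nothing makes the conclusion depend on them.

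**Conclusion.** The point holds in a limited form. The protocol's own wording calls the FAS a measure of overall fatigue in one place and of work-related fatigue in another. Hypothesis 1 rests on a joint test that cannot separate the two, followed by tests within arms. A FAS-only effect could therefore be reported as an effect on work-related fatigue.

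The possibility follows from the form of the test. How often it would happen depends on the assumed effect and correlations: about 36% to 66% at 0.4 SD and 71% to 96% at 0.6 SD, given 45 per arm, equal correlations of .3 to .7, and exactly zero effect on the other two scales.

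A reader might infer that the trial is likely to reach a false primary conclusion. The documents do not support that: they give no reason to expect a FAS-only effect, and the randomised comparison on each scale remains valid. The weakness is in the step from a significant joint test to a statement about work-related fatigue.

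**What to change.** In Analyses of primary and secondary outcomes:

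1. Keep the three-indicator RM-MANOVA as the primary test.
2. After a significant interaction, test condition x time between arms for each scale separately. Paired t-tests may stay as description.
3. State that a reduction in work-related fatigue is concluded only if emotional exhaustion or need for recovery differs between arms in the expected direction, and that an effect on the FAS alone is reported as an effect on overall fatigue.

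Use the same label for the FAS in Participants and recruitment and in Primary outcome measures. The entry criteria need not change.

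No new data are needed. The cost is the power loss shown for Option B: small when the three scales move together, substantial when the work-anchored scales move only half as much as the FAS. The authors should accept that loss knowingly, since it is the price of a conclusion specific to work.

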### Statistical analyses

#### Sample size

Based on previous research, it is difficult to predict an exact effect size on which we can base our sample size, given that these studies report small to large effect sizes [19, 20, 22, 23], and that they differ in design (i.e., duration of exercise intervention; absence of control condition) and target audience (i.e., low to clinical levels of work-related fatigue). Since we conduct our study among employees with high but no clinical levels of work-related fatigue (we expect a decrease in work-related fatigue, but not as large as we would expect among employees with clinical levels) and our intervention is relatively short, we expect a small to medium effect size. To determine sample size, a power analysis has been conducted in the statistical program G*power [79]. This analysis was based on a repeated measures ANOVA with work-related fatigue as within subjects factors and condition as between subjects factor. This analysis showed that a total of 90 participants was required in order to detect a small to medium effect of .15 on the primary outcome work-related fatigue from pre to post intervention, given a two-sided 5 % significance level, a power of 80 %, and an correlation of .05 across repeated measures [80]. Because we anticipated a dropout rate of about 20 %, we intend to recruit 108 participants.

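### Hypothesis 1 claims a reduction in fatigue, but the planned three-outcome MANOVA has no sign and no planned follow-up gives a signed between-arm result for each scale

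*Protocol article*

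**What the plan says.** All references are to the protocol article.

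- **Hypothesis 1** (Background, Exercise and work-related fatigue) is directional: "the exercise intervention is effective in reducing work-related fatigue".
- **Primary outcome** (Work-related fatigue): "We will use three self-reported indicators to measure work-related fatigue". These are emotional exhaustion, overall fatigue and need for recovery. On each, a higher score means more fatigue.
- **Test** (Analyses of primary and secondary outcomes): "We will conduct a RM-MANOVA for the three indicators of work-related fatigue together". Interest lies in the condition by time interaction because "this indicates that the conditions differ from each other with respect to the development of the outcome measure over time".
- **Follow-up** (same section): "If applicable, significant interactions will be further examined by paired-sample t-tests". The effect size is partial eta-squared. A chi-square test also compares the arms on the proportions below the emotional exhaustion and overall fatigue cut-offs.
- **Sample size**: "This analysis was based on a repeated measures ANOVA with work-related fatigue as within subjects factors and condition as between subjects factor", that is, one outcome, not three.

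**The concern.** With a single outcome, a two-sided test is enough for a directional claim, because the sign of the estimate settles direction. With three outcomes, the omnibus statistic measures how far the vector of arm differences lies from zero and carries no sign. The article does not say which pattern across the three scales would confirm Hypothesis 1.

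The other planned analyses do not fill the gap:

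- **Paired t-tests** look at change within one arm. Participants are selected for high scores on two of the three scales, and those screening scores serve as T0, so regression to the mean can lower both arms. Under Strengths and limitations the article itself allows for a fall on the wait list. A significant fall in the exercise arm is therefore not evidence of a difference between arms.
- **Partial eta-squared** is the same for benefit and harm of equal size.
- **The chi-square test** compares arms, but it leaves out need for recovery, for which no norm score exists, and it is not tied to Hypothesis 1.

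At stake is whether a significant primary result can be reported as reduced fatigue.

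**Working it through.** **1. The plan's own figure.** Inputs from Sample size: effect .15 (read as Cohen's f), two-sided 5%, 80% power, N = 90, two measurements. For the interaction, λ = f² × N × 2 / (1 − ρ), with F(1, N − 2).

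- ρ = .5: λ = 0.0225 × 90 × 2 / 0.5 = 8.1, power 80.4%. This reproduces 90.
- ρ = .05 as printed: λ = 0.0225 × 90 × 2 / 0.95 = 4.26, power 53%. The N needed would be 168.

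The mismatch in ρ is a separate matter. It matters here only for the effect on the change score, d = 2f√(2/(1 − ρ)), which is 0.60 SD at ρ = .5 and 0.44 SD at ρ = .05.

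**2. The planned test.** With two arms and two times, the multivariate interaction equals Hotelling's T² on three change scores: F(3, N − 4) with λ = (N/4) δ′Σ⁻¹δ. Here δ holds the three arm differences in SD units of change, and Σ has a common correlation r. The article gives no r, so it is assumed and varied. N = 86 is 108 × 0.8 after the anticipated dropout, so N/4 = 21.5.

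**3. Direction.** λ is unchanged when δ becomes −δ. At every r, uniform worsening is exactly as likely to be significant as uniform improvement of the same size.

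**4. Concordant against opposing effects of equal size d.**

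- All three improve: λ = 21.5 × 3d²/(1 + 2r).
- One improves, one worsens, one unchanged: λ = 21.5 × 2d²/(1 − r).

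The two are equal when 3(1 − r) = 2(1 + 2r), that is, r = 1/7. For d = 0.3:

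| r | All improve: λ, significant | Opposing: λ, significant |
|---|---|---|
| 0 | 5.81, 48% | 3.87, 33% |
| .3 | 3.63, 31% | 5.53, 46% |
| .5 | 2.90, 26% | 7.74, 61% |
| .7 | 2.42, 22% | 12.90, 85% |

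If the worsening is only half as large as the improvement, the opposing term becomes [1.25 − 0.25r/(1 + 2r)]/(1 − r). It exceeds 3/(1 + 2r) only when r > 1/3, where both equal 1.8. A simulation at N = 90, r = .5, d = 0.3 gave 26.7% and 63.9%, against 26.7% and 63.8% from the formula.

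**5. A 1-df composite as the alternative.** For the mean of the three standardised changes, λ = 21.5 × (mean of δ)² × 3/(1 + 2r), with F(1, N − 2). At r = .5:

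| Effects (SD, benefit positive) | MANOVA: λ, power | Composite: λ, power |
|---|---|---|
| .6, .6, .6 | 11.61, 81% | 11.61, 92% |
| .6, .4, .2 | 8.60, 67% | 5.16, 61% |
| .6, .6, 0 | 15.48, 91% | 5.16, 61% |
| .6, 0, 0 | 11.61, 81% | 1.29, 20% |

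The ranking also depends on r: for (.6, .4, .2) at r = .3 the composite has 71% and the MANOVA 68%.

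**The case against.** The case for the plan has four parts.

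- **Power at the planning effect is adequate.** If the pre-post correlation is read as .5, the planning effect is 0.6 SD on change, and the MANOVA has 81% for a uniform effect at N = 86 and r = .5. This stands. (With .05 as printed, the effect is about 0.44 SD and power about 50%, but that is a sample-size matter.)
- **Truly opposing effects are unlikely.** Nothing in the article suggests that exercise would improve one fatigue scale and worsen another. Under no effect at all, the error rate is nominal (4.7% in a simulation at 43 per arm). Both points stand. The opposing pattern shows what the test responds to; it is not a forecast.
- **The follow-up tests would reveal mixed directions.** This stands in part. The paired t-tests would often show them, but within arms, and the between-arm chi-square covers two of the three scales.
- **Reading rules belong in an analysis plan.** This is fair for detail. But the article itself fixes the primary test, the within-arm follow-up and the unsigned effect size, and those choices do not match the hypothesis.

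A reader might also infer that the MANOVA loses power for whatever the trial expects, and so should give way to a composite. The documents do not support that. They predict a reduction, not equal reductions on all three scales, and when benefits are unequal or partial the MANOVA can be the stronger test.

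**Conclusion.** The point holds as a mismatch between a directional hypothesis and an unsigned primary test without a signed between-arm follow-up for every scale. That a significant result alone cannot support a reduction is true at every r and needs no assumption about effect size.

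The preference for opposing over concordant effects is conditional: 46% to 85% against 31% to 22% for 0.3 SD effects, with r assumed between .3 and .7, a common correlation and 86 analysed. Positive correlation is plausible for three indicators of one construct, but the article gives no value. It would be wrong to say without conditions that the MANOVA favours contradictory results: with equal opposing effects this needs r above 1/7, and at r = 0 the order reverses.

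The plan should be amended on how Hypothesis 1 is read. The point is not grounds for discarding the MANOVA.

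**What to change.** 1. Replace the within-arm paired t-tests for the primary outcome with the between-arm difference at T6, adjusted for T0, and its 95% CI for each of the three indicators.
2. State that Hypothesis 1 is supported only when the MANOVA interaction is significant, the between-arm estimates favour exercise and none indicates worsening.
3. Define worsening in advance, by the sign of the estimate or by an interval wholly on the harmful side. The choice matters: a strict sign rule would fail about half the time on a scale that exercise truly leaves unchanged.
4. Report these signed differences beside partial eta-squared.

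This uses the same data and changes only the analysis wording. The cost is a somewhat stricter condition for claiming success, which is small if all three scales truly improve by 0.6 SD: the standard error of a difference in change is about √(4/86) = 0.22 SD, so such an effect lies nearly three standard errors from zero.

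A 1-df composite of the standardised indicators, as sole primary test, is an option. It matches the univariate sample-size model and has a sign. It should be chosen only if near-equal benefits are expected, because of the losses shown above for unequal or partial benefit. The three between-arm intervals would still be needed beside it, since one scale can drive a composite while another worsens.

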*Switching* refers to the ability to shift between tasks [68], and will be assessed by the Matching Task [70, 71]. In this task, four different geometric figures (a circle, a hexagon, a square, and a triangle), presented in the colors blue, green, red, or yellow are used as stimuli. The task consists of 31 task runs, each consisting of on average six trials (range: 4–8 trials). During a trial, a colored reference figure is displayed in the upper half of the screen, and four colored match figures are shown in the lower half of the screen. Participants will be instructed to match the reference figure to one of the match figures according to shape or color. Whether participants have to match according to shape or color, will be randomly chosen and indicated by a cue that is displayed for 1000 ms. Participants can push one of four buttons on the keyboard which corresponds to one of the four match figures in the lower half of the screen. During one single task run, participants have to match either according to color or shape. The color-shape combinations are shown in a way that there is one ‘right’ option. Half of all task runs consisted of ‘switch’ runs, in which the type of cue differs from the previous run. The other half consists of ‘repetition’ runs, in which the type of cue is identical to the previous run. The duration of the test is approximately six minutes. Both the mean reaction time for switch runs and repetition runs will be used as an outcome measure for switching (for more detailed information about this task, see [70]).

*Inhibition* addresses one’s capability to deliberately inhibit dominant and automatic responses to certain stressors [68]. Inhibition will be measured with the Sustained-Attention-to-Response Test (SART [72]). During this test, digits (ranging from 1–9) are displayed one-by-one in the centre of the screen. Participants are instructed to push a button on a button-box when a digit appears on the screen, except when the digit is a ‘3’, which occurs in 11.1 % of the cases. A total of 450 digits will be presented, each with a duration of 250 ms. The interval between digits is 850 ms. The number of inhibition errors (thus, when a participant presses the button when a ‘3’ appears on the screen), will be taken as a measure for inhibition.

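### For the Matching Task, the interaction the plan singles out (condition x time) measures general response speed; the term specific to switching, condition x time x run type, has no stated role

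*Protocol article*

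**What the plan says.** Under Cognitive functioning, the protocol article says that switching "refers to the ability to shift between tasks". It describes two kinds of task run. On the first: "Half of all task runs consisted of ‘switch’ runs, in which the type of cue differs from the previous run". On the second: "The other half consists of ‘repetition’ runs, in which the type of cue is identical to the previous run". It then fixes the score: "Both the mean reaction time for switch runs and repetition runs will be used as an outcome measure for switching". It defines no difference between the two means (switch cost).

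Under Analyses of primary and secondary outcomes, the Matching Task gets its own model: a mixed ANOVA with run type and time as within-subject factors and condition as between-subject factor. The next sentence reads "In all analyses, we are particularly interested in the ‘condition x time’ interaction", on the ground that this term shows whether the arms develop differently over time. The only further step is that, where applicable, "significant interactions will be further examined by paired-sample t-tests". The condition x time x run type interaction is not named anywhere in the article.

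**The concern.** For the other outcomes, which are analysed in 2x2 models, condition x time is the right term. The Matching Task is different because run type is a third factor, and condition x time averages over it. A repetition run keeps the rule of the previous run, so it requires no shift. An average of switch and repetition runs therefore mixes the ability to shift with everything else that makes a person respond faster, such as motor speed, effort and practice.

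Two errors become possible. Participants know their condition (Strengths and limitations states that the study is not blinded), so a general speed-up in the exercise arm is plausible without any change in switching, and condition x time would respond to it. Conversely, a benefit confined to switch runs is halved in the average and compared with the variability of overall speed, so it is harder to detect. Both bear on the switching part of Hypothesis 2f.

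**Working it through.** The plan gives no figure for this task, so there is none to reproduce. The design point is algebra; the rates below are illustrations.

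**What each term tests.** For each person, let S and R be the pre-post changes in mean reaction time on switch and repetition runs. With two-level factors:
- the condition x time F is the square of the two-sample t on (S + R)/2;
- the condition x time x run type F is the square of the two-sample t on S - R.

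Run type cancels out of the first. Only the second is the change in switch cost. No assumed value is needed for this.

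**Inputs for the illustration.**
- From the protocol article: 108 recruited, 1:1 allocation, about 20% dropout, two-sided 5% (stated for the primary outcome, assumed here too). Analysed N = 108 x 0.8 = 86.4, taken as 86.
- Assumed: S and R have equal variance v and correlation r. This r is the correlation between change scores, not between raw reaction times. Range shown: .5 to .95.

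**Formulas.**
- SD of (S + R)/2 = sqrt(v(1 + r)/2).
- SD of S - R = sqrt(2v(1 - r)).
- Power from the noncentral F with 1 and 84 degrees of freedom, noncentrality N d²/4, where d is the arm difference divided by the SD of the contrast.

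**(a) Equal speed-up in ms on both run types, switch cost unchanged.**
- d = 0.6 on the average: noncentrality 86 x 0.36/4 = 7.74, so condition x time is significant in 78.5% of trials.
- d = 0.3: noncentrality 1.935, significant in 28%.
- The three-way term is under its null in both cases: 5%.

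**(b) Benefit on switch runs only, sized for 80% power on the three-way term.** This needs d = 0.61 on S - R (noncentrality 8.00). A gain of D on switch runs changes S - R by D but the average by D/2. The standardised effect on the average is therefore 0.61 x sqrt((1 - r)/(1 + r)).

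| r (change scores) | d on average | Power, condition x time |
|---|---|---|
| .95 | 0.098 | 7.3% |
| .90 | 0.140 | 9.8% |
| .80 | 0.203 | 15.4% |
| .69 | 0.261 | 22% |
| .60 | 0.305 | 29% |
| .50 | 0.352 | about 37% |

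**Second check, by simulation** (5000 trials per scenario; assumed person SD 120 ms, person-by-occasion SD 60 ms, residual SD 40 ms, switch cost 200 ms). These SDs imply a change-score correlation of 60²/(60² + 40²) = .69.
- Uniform speed-up of 30 / 50 / 70 ms: condition x time significant in 32 / 70 / 94% at N = 90 and 37 / 79 / 97% at N = 108; the three-way term stays at about 5%.
- Fall of 40 ms in switch cost only: condition x time 16% (N = 90) and 19% (N = 108), against 66% and 72% on the three-way term.
- Switch runs 20 ms faster and repetition runs 20 ms slower: condition x time about 5%, the three-way term 65% and 72%.
- No effect: about 5% on both terms.

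**The case against.** The strongest reply is that the plan expresses emphasis, not exclusivity. Being particularly interested in one term does not forbid reading another. Adding run type as a factor has little purpose unless its interactions are read, the three-way term is standard output of the stated model, and the sentence on following up significant interactions is not restricted to condition x time. This stands as a limit on the claim. A reader might infer that condition x time is the sole or decisive test of switching; the text does not say so. What remains is that the plan names one term, in a sentence that covers all analyses and directly follows the Matching Task model, and gives the switching-specific term no role. The follow-up t-tests are not said to compare switch cost between arms.

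A reader might also infer that a faster exercise arm will be reported as better at switching. No passage says that, and Hypothesis 2f speaks of cognitive functioning as a whole. It is a possible reading, left open because both reaction times are called outcome measures for switching. The plan also collects ratings of motivation, effort, demand and fatigue around the tests. They would help to interpret a general speed-up, but they do not change which contrast is tested.

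It would also be too strong to say that a true fall in switch cost is nearly invisible on condition x time. That holds only when the two change scores are very highly correlated; at .5 the power is about 37%.

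Finally, a condensed article may leave detail to an analysis plan. But this is not a missing detail: the article states its term of interest, and for this task that term does not isolate the construct.

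**Conclusion.** The point holds in a limited form. For the Matching Task, the emphasised interaction is the arm difference in change of average reaction time. The term matching the article's own definition of switching is in the model without a stated role. This is exact and rests on no assumed value.

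The size does rest on assumptions, since the article gives no SD or correlation for the task. At N = 86, a pure speed-up gives 28% (0.3 SD) to 79% (0.6 SD) significant results on condition x time, against 5% on the three-way term. A switch-only benefit with 80% power on the three-way term has about 7-37% power on condition x time for change-score correlations of .95 down to .5. Scenario (a) takes the speed-up as equal in ms on both run types; a proportional speed-up would also shrink switch cost in ms and so would not leave the three-way term at 5%.

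The consequence is confined to one of four cognitive indicators within one of five secondary outcomes. The primary outcome and the sample size are not touched.

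**What to change.** In Analyses of primary and secondary outcomes, add one sentence after the Matching Task model: the test of switching is condition x time x run type. Testing the arm difference in pre-post change of switch cost (switch minus repetition mean reaction time) gives the identical result. The arm effect on T6 switch cost adjusted for T0 switch cost addresses the same question and could be named instead, but one of them should be fixed in advance. State also that condition x time averaged over run type will be reported as general response speed and not as evidence on switching. Under Cognitive functioning, define switch cost as the score for switching, so that the repetition-run mean is not by itself labelled a switching outcome.

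The cost is a sentence or two. No new data are needed, and the model already specified gives the three-way term.
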